#### Analysis of differential intervention effects

To test for differential effects of the intervention for specific subgroups of women, we will either enter a grouping variable (e.g., rural/urban) and its three-way interaction with intervention group and time, or, if subgroups are reasonably large, we will analyze differences in intervention effects using multi-group analysis techniques. These analyses are not fully powered; therefore, we will interpret differences in effect sizes across the specific subgroups rather than rely on statistical significance. Subgroups to be examined include geographic location (rural/urban), partner status (separated from partner or not), continuing exposure to abuse (yes/no), mothering (yes/no), Indigenous identification (yes/no).

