However, few interventions have been shown to improve the safety, health or quality of life of women experiencing IPV. Safety planning, including education to increase women’s awareness about IPV, and personalized support to identify options for reducing risks and support for accessing resources, is one of the most widely recommended IPV interventions [9]. There is evidence from systematic reviews that providing information and support to engage women in safety planning and accessing services that meet their needs reduces both physical and psychological violence [9, 10], but the effects on women’s mental health and well-being are unknown. Although violence-specific services are a key source of help with safety planning, fewer than 1 in 5 Canadian women who experience IPV access such services [11]. Rural, Aboriginal, racialized and immigrant women, women with partners other than men, and those who prioritize privacy (including more affluent women) face unique safety risks and barriers to accessing information and support for safety planning [12–15]. Effective, accessible, personalized interventions are needed to support women’s capacity to engage in actions to promote their safety and well-being, and potentially, to improve their sense of confidence, control and mental health.

Effective online health interventions have been developed in varied domains, including smoking cessation, depression, anxiety and sexual health [16–18]. Evidence shows that interaction, feedback, and tailoring are important features of these online interventions [17]. For women experiencing IPV, personalized, online interventions could improve access to information and support for safety planning and well-being, particularly for women who are reluctant or unable to access formal resources. In a recent pilot test of the first interactive, online safety decision aid for women experiencing IPV, called IRIS, Glass, Eden, Bloom and Perrin [19] found that women’s safety planning increased and decisional conflict decreased immediately after one use of this resource. The effectiveness of IRIS in improving the mental health of women exposed to IPV was recently tested in a randomized controlled trial in the United States [20], the results of which are pending. Two other variations of this online intervention (isafe and I-DECIDE) are currently being tested in randomized controlled trials in New Zealand [21] and Australia [22].

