#### Testing the mechanisms that explain the interventions effects

To better understand how the intervention achieves its effects, we will employ structural equation modeling (SEM) techniques for longitudinal data to test a theoretical model specifying the relationships between change in the intervention, a set of mediating variables (decisional conflict, safety strategies, support, mastery, abuse severity) and women’s mental health. Latent variables will be developed for each construct from existing manifest variables. Goodness of fit between the model and the data will be assessed. The repeated measures character of the data will be integrated in the model by specifying latent growth curve trajectories for the outcome and some of the mediating variables.

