## Discussion

This trial builds on and extends research on online safety interventions for women experiencing IPV in three key ways. First, the intervention tested in this study integrates increased attention to both health and emotional safety – both during completion of the online intervention and in the strategies offered to women as part of the intervention. Second, building on lessons learned from IRIS, we have streamlined data that will be collected from the control group women (e.g., no completion of the Danger Assessment), in an effort to reduce any measurement effects. Finally, we will be able to test for effects in a range of specific contexts, including varied geographies, women who have and have not separated from their abusive partners and who are/are not experiencing ongoing violence. Therefore, study findings will contribute timely evidence about the effectiveness of online safety and health interventions appropriate for diverse life contexts. Moreover, this study will produce contextualized knowledge about how women engage with the intervention; its strengths and weaknesses; whether specific groups benefit more than others; and the processes that explain any positive outcomes. If effective, this information is critical for successful scale up of complex interventions, such as *iCAN*, into health and social services and/or for public access for women who prefer to work through the intervention independently.

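### Low power is given as the reason to interpret subgroup differences in effect size, although it makes them noisier, and the continuing-abuse and partner-status subgroups have no stated time point

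*Protocol article*

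**What the plan says.** Under Analysis of differential intervention effects, the protocol article offers two methods: a model with a grouping variable and "its three-way interaction with intervention group and time", or multi-group analysis if subgroups are large enough. It then states "These analyses are not fully powered" and, as the consequence, "we will interpret differences in effect sizes across the specific subgroups rather than rely on statistical significance".

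Five binary factors are named: rural or urban location, then "partner status (separated from partner or not), continuing exposure to abuse (yes/no), mothering (yes/no), Indigenous identification (yes/no"). No time point is given for any of them.

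Four other sections bear on this:

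- **Participant inclusion criteria:** every woman must report partner abuse in the 6 months before entry.
- **Data collection:** abuse severity is measured at every visit, and demographic data may be updated at later waves.
- **Testing the mechanisms that explain the interventions effects:** the model includes "a set of mediating variables (decisional conflict, safety strategies, support, mastery, abuse severity"). Background cites review evidence that safety planning "reduces both physical and psychological violence".
- **Objectives and Discussion:** the Objectives present the subgroup aim as exploratory. The Discussion says "Finally, we will be able to test for effects in a range of specific contexts", naming separation and ongoing violence among them, and ties knowledge of who benefits more to scale-up.

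**The concern.** There are two separate problems.

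**The interpretation rule.** Lack of power is a reason to trust an observed subgroup difference less. The plan uses it as the reason to read the difference directly. This is a stated rule, not a detail left for later, and followed as written it invites readers to take chance differences for differential benefit. The results are meant to inform scale-up, so rural or Indigenous women, for example, could be described as benefiting more or less on the strength of noise.

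**The timing of two subgroups.** All participants were abused shortly before entry, so a woman whose abuse is not continuing is readily understood as one whose abuse stopped during follow-up. If follow-up abuse defines the groups, and the intervention affects abuse as the mediation model supposes, the women in a given stratum are no longer comparable between arms. Partner status has the same weakness if a later, updated value is used.

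**Working it through.** **Inputs from the protocol article (Number of participants required).** 450 women, 1:1; 10% attrition at 12 months; planning effect sizes 0.29 and 0.52. The retained sample reproduces: 450 × 0.9 = 405. No power or precision figure is given for the subgroup analyses, so there is none to reproduce.

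**Assumptions.** The article gives no subgroup shares, so splits from 50/50 to 10/90 are shown. Arms are balanced within subgroups. The base case uses the standard error of an unadjusted comparison at one time point, in SD units.

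**Chance differences between subgroups.** Let f be the share in the smaller subgroup. Women per arm are n1 = 405f/2 and n2 = 405(1 − f)/2.

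SE of the difference between the two subgroup effects = √(2/n1 + 2/n2).

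Chance of a gap of at least 0.29 SD with no true heterogeneity = 2 × [1 − Φ(0.29/SE)].

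| Split | n1, n2 per arm | SE | 95% CI half-width | Chance of gap ≥ 0.29 |
|---|---|---|---|---|
| 50/50 | 101.25, 101.25 | 0.199 | 0.39 | 14.5% |
| 30/70 | 60.75, 141.75 | 0.217 | 0.43 | 18% |
| 20/80 | 40.5, 162 | 0.248 | 0.49 | 24% |
| 10/90 | 20.25, 182.25 | 0.331 | 0.65 | 38% |

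For example, at 50/50: √(2/101.25 + 2/101.25) = 0.199; 0.29/0.199 = 1.46; two-sided tail 14.5%. Even in this best case the interval on a subgroup difference is wider on each side than the whole lower planning effect. Power to detect a true 0.29 SD interaction at two-sided 5% is 31% at 50/50 and 14% at 10/90.

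**Sensitivity to the analysis model.** The planned contrast is change over time in a GEE, and its precision depends on a within-person correlation r that the article does not give.

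- For a simple change score, the SE is multiplied by √(2(1 − r)). This is 1 at r = 0.5, so the table is unchanged. At r = 0.3 the multiplier is √1.4 and the chances become 22% (50/50) and 46% (10/90). At r = 0.7 it is √0.6 and they become 6% and 26%.
- For baseline adjustment at r = 0.5, the multiplier is √0.75 and the chances are 9% and 31%.

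**Several factors.** If the five factors were independent, the chance of at least one such gap on one outcome would be 1 − (1 − 0.145)^5 = 54% with all splits at 50/50, and 1 − (1 − 0.243)^5 = 75% with all at 20/80. These figures are illustrative only, because both the shares and the independence are assumed.

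**Grouping on follow-up abuse.** A simulation of 2 million women had no intervention effect on the outcome. The intervention lowered exposure from 60% to 50% or 40%, and underlying severity correlated 0.3 or 0.5 with the latent liability to exposure. Intervention-minus-control differences within strata were:

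| Exposure in intervention arm | Correlation | Still exposed | No longer exposed |
|---|---|---|---|
| 50% | 0.3 | 0.045 | 0.052 |
| 50% | 0.5 | 0.074 | 0.085 |
| 40% | 0.3 | 0.095 | 0.096 |
| 40% | 0.5 | 0.158 | 0.158 |

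The overall difference was zero in every case. Spurious effects of about 0.05 to 0.16 SD therefore appear within both strata. In this model they are nearly equal, so they distort each stratum's effect much more than the difference between strata.

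**The case against.** The case for the plan has real weight.

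- **Uncertainty is not excluded.** A reader might infer that subgroup differences will be read with no regard to uncertainty. The text does not say so. Not relying on significance is compatible with confidence intervals, one of the two methods is an interaction model, and interval reporting may be set out in an analysis plan that is not shown. The aim is worded as exploratory, limited power is admitted, and the factors are named in advance. All of this stands. What remains is the stated reasoning, which is wrong whatever is reported beside it.
- **Post-randomisation grouping is not stated.** Abuse and demographics are also collected at baseline, and at entry some women's abuse may have stopped while others' had not, so a baseline reading is possible. Baseline abuse status as a moderator and later severity as a mediator can coexist. This stands: the bias is a supported risk that arises from missing timing, not a certainty.
- **Separation is not shown to be a target of the intervention.** It is neither a listed outcome nor a mediator, and women choose their own relationship plan. For partner status the concern is limited to the use of updated values.
- **A threshold of 0.29 is this review's choice.** The plan does not say a gap of that size would be declared differential benefit, so it does not follow that a false subgroup claim is the likely result.
- **The Discussion does not strictly contradict the Methods.** An underpowered test is still a test. The difference is one of tone.

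**Conclusion.** The point holds in a limited form. Low power does not justify interpreting differences in subgroup effect sizes. With 405 women and no true heterogeneity, a gap as large as the lower planning effect arises in about 15% (50/50) to 38% (10/90) of single comparisons. That range rests on assumed shares and an unadjusted single-time-point standard error. Over the other models and correlations tried, it runs from 6% to 46%.

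The time point of the continuing-abuse subgroup needs to be fixed, because the article itself treats abuse as something the intervention may change. Partner status needs the same if updated values could be used. A reader might go further and infer that post-randomisation bias would itself create false findings about who benefits. The simulation does not support that: under its assumptions the bias falls on the within-stratum effects and largely cancels in the contrast between strata.

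The primary comparison is unaffected. This is a correction that should be made before the subgroup results are interpreted.

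**What to change.** 1. Define the continuing-abuse and partner-status subgroups from baseline data only, and state the baseline item and recall period used. Keep follow-up abuse for the mediation analysis.
2. Replace the interpretation rule: for all five factors, report the arm by subgroup (by time) interaction estimate with its 95% confidence interval, interpret it in the light of that interval, and call the results hypothesis-generating. A rule barring any statement when the interval includes zero is not needed. It would be a significance test in another form, which the authors could reasonably decline.
3. Word the Discussion to match, so that it speaks of exploring effects across contexts with limited precision.

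The changes need no further participants or measurements. The cost is that fewer subgroup statements can be made, or that they must be more cautious.

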#### Testing the mechanisms that explain the interventions effects

To better understand how the intervention achieves its effects, we will employ structural equation modeling (SEM) techniques for longitudinal data to test a theoretical model specifying the relationships between change in the intervention, a set of mediating variables (decisional conflict, safety strategies, support, mastery, abuse severity) and women’s mental health. Latent variables will be developed for each construct from existing manifest variables. Goodness of fit between the model and the data will be assessed. The repeated measures character of the data will be integrated in the model by specifying latent growth curve trajectories for the outcome and some of the mediating variables.

### Process evaluation

In-depth qualitative interviews will be conducted with a sub-sample of approximately 60 women after they have completed the trial to explore how they engaged with the intervention; their perceptions of intervention strengths and weaknesses, risks and benefits, and helpfulness; and processes of change that may explain intervention effects. At the end of the 12-month study visit, all participants (both groups) will be asked to indicate their interest in participating in a qualitative interview about their experiences taking part in the study, and to provide permission for a RA to contact them using their safe email address. Maximum variation sampling will be used to identify and recruit a sample of women with varied sociodemographic backgrounds (e.g., age, whether they are mothers, geographic location) and histories with their partners (e.g., abuse history, partner gender, living with partner versus separated) from those who consent to be contacted. A RA will contact these women to provide information about the interview process, seek separate informed consent and to arrange a time for the interview. Interviews will be conducted by an investigator or trained RA by telephone or Skype using existing study protocols for safe contact. A structured interview guide will be used to explore how women engaged with the online interventions and how information or resources were used; positive and negative aspects and impacts; and how the context of women’s lives shaped their intervention use and impacts. Interviews will be audio-recorded and transcribed verbatim and analyzed using content analysis techniques.

The process evaluation will also draw on data collected in the 12-month exit survey offered to all women, administrative (use) data collected by the online system (both groups), and report of helpfulness of the online interventions in supporting women’s decision making (collected at baseline and 3, 6, and 12-month study visits using the Preparation for Decision-Making Scale previously described) in order to fully develop, explain, and contextualize the findings.

## Discussion

This trial builds on and extends research on online safety interventions for women experiencing IPV in three key ways. First, the intervention tested in this study integrates increased attention to both health and emotional safety – both during completion of the online intervention and in the strategies offered to women as part of the intervention. Second, building on lessons learned from IRIS, we have streamlined data that will be collected from the control group women (e.g., no completion of the Danger Assessment), in an effort to reduce any measurement effects. Finally, we will be able to test for effects in a range of specific contexts, including varied geographies, women who have and have not separated from their abusive partners and who are/are not experiencing ongoing violence. Therefore, study findings will contribute timely evidence about the effectiveness of online safety and health interventions appropriate for diverse life contexts. Moreover, this study will produce contextualized knowledge about how women engage with the intervention; its strengths and weaknesses; whether specific groups benefit more than others; and the processes that explain any positive outcomes. If effective, this information is critical for successful scale up of complex interventions, such as *iCAN*, into health and social services and/or for public access for women who prefer to work through the intervention independently.

### Trial status

Active follow up.

## Abbreviations

IPV: Intimate partner violence
iCAN: iCAN Plan 4 Safety
RA: Research assistant
PTSD: Post-traumatic stress disorder
DA: Danger Assessment
